### Baseline eligibility assessment

Adherence will be measured electronically for 3 months prior to the first intervention to determine study eligibility and obtain a baseline, pre-intervention measure of medication adherence. The participant’s medication(s) and dosing schedule is determined by first reviewing the patient’s medical record and then confirming the medications with the patient. The study coordinator will record these data into the AdhereTech system. Participants will place their glaucoma medications inside AdhereTech electronic medication monitors that look like pill bottles. Patients will have different monitors for each of their glaucoma medications. Each time a bottle is opened, and the time and date are recorded. These records will be collected in real time and transmitted through the cellular data network so that adherence to medications can be calculated at any time interval (weekly, biweekly, monthly, etc.). The study coordinator will record each participant’s adherence data in the medical record during their study visits.

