Validated measures will be used to assess these proposed mediators of adherence. Skills will be measured with five constructs: perceived competence, glaucoma knowledge, self-efficacy, goal setting, and confidence asking the physician questions. Perceived competence [59] (four items, Cronbach *α* = 0.80) assesses participants’ perceptions of how able they are to manage their glaucoma on a seven-point Likert scale. Perceived competence will be measured at the baseline, 6-, 12-, and 24-month study visits. Glaucoma Knowledge will be assessed with a 10-item true/false test generated by the National Eye Institute (NEI) [60]. Glaucoma knowledge will be measured at the 3- and 8-month study visits, before and after the eyeGuide intervention, respectively, and at the 24-month study visit. Glaucoma medication and eye drop instillation self-efficacy [61] (medication self-efficacy, 10 items, eye drop instillation self-efficacy, 6 items, *α* = 0.91 for all 16 items) assess participants’ self-confidence in using their eye drop medications as prescribed and instilling them into their eyes correctly using a three-point Likert scale. Glaucoma medication and eye drop instillation self-efficacy will be measured at the baseline, 6-, 12-, and 24-month study visits. Goal setting (three items, *α* = 0.80) measures whether or not health care providers asked participants to set goals to improve how they take care of their chronic disease on a five-point Likert scale. The Goal Setting Scale is a sub-scale of the Patient Assessment of Chronic Illness [62] measure. We could not use the full sub-scale as the final two questions ask if the person has been asked to attend a class to help cope with their chronic condition or asked to fill out a survey about their chronic condition, neither of which are standard aspects of current glaucoma care. Goal setting will be measured at the baseline study visit, and the 12- and 24-month study visits. Confidence asking the physician questions will be measured with three items from the adapted Perceived Efficacy in Patient-Physician Interactions Scale [63] (PEPPI, five items, α = 0.83) using a five-point Likert scale. Confidence asking the physician questions will be assessed at the baseline visit and the 12-month study visit.

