LMMs will be used to investigate predictors of adherence. Variables investigated will include participant characteristics and demographics, clinical measures of disease severity, and counseling and health literacy measures. Repeated measures logistic regression with generalized estimating equations (GEE) will also be used to investigate predictors of adherence >/=80%. The repeated measures analyses (LMM and GEE) will use adherence data gathered over all time points and account for the correlation within an individual over time. Moderators of glaucoma medication adherence will be investigated in the LMMs by interactions with time, to test the hypothesis that moderators will have different slopes of medication adherence over time [83]. Mediators of glaucoma medication adherence will be investigated with a series of LMMs [83]. First, the effect of the intervention on glaucoma medication adherence will be tested. Because all participants receive the intervention, this will be a test of slope of medication adherence over time (*Y*_medication adherence_ ~ *X*_time_). Next, the effect of the intervention on glaucoma medication adherence after adjustment for a mediator will be tested (*Y*_medication adherence_ ~ *X*_time_ + *X*_mediator)_. Lastly, the effect of the intervention on a mediator will be tested (*Y*_mediator_ ~ *X*_time_). After standardizing the effects from these three models, the direct, indirect, and total effects of the intervention will be estimated and Sobel’s test will be used to test the significance of the indirect effect.

We will adjust for weekly and seasonal trends when assessing other factors influencing adherence. We will use time series analysis using the 2 years of daily adherence data for each patient. Using Unobserved Component Models (UCMs), weekly and seasonal (yearly) cycles will be identified and tested in the context of a comprehensive regression model that adjusts for covariates such as participant characteristics and study intervention period. After adjustment, we will test for trends, e.g., a gradual improvement in adherence over time or a drop in adherence post-intervention [84, 85]. The SAS procedures TIMESERIES and UCM will be used for these analyses. The UCM procedure handles missing values in the dependent series and provides model diagnostics.

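### Total and direct effects in the mediation analysis come from different records, because adherence is available throughout but each mediator only at two to four visits

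*Protocol article*

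**What the plan says.** The Data analysis section of the protocol states: "Mediators of glaucoma medication adherence will be investigated with a series of LMMs". Three models follow.

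- Total effect: adherence ~ time. "Because all participants receive the intervention, this will be a test of slope of medication adherence over time".
- Direct effect: adherence ~ time + mediator. "Next, the effect of the intervention on glaucoma medication adherence after adjustment for a mediator will be tested".
- Effect on the mediator: mediator ~ time.

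The coefficients are standardized, "the direct, indirect, and total effects of the intervention will be estimated", and the indirect effect is tested with Sobel's test. On the data to be used, the same section says: "The repeated measures analyses (LMM and GEE) will use adherence data gathered over all time points".

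Adherence is recorded continuously for two years. On the monitor records, the Baseline eligibility assessment section says: "These records will be collected in real time and transmitted through the cellular data network". The mediators are not continuous. From the Secondary outcomes section and Table 2 with its footnote, the schedules in months are:

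- 0/6/12/24: perceived competence, self-efficacy, HCCQ, TSRQ, glaucoma-related distress, barriers, and the hopefulness, confidence and motivation rulers
- 0/12/24: goal setting ("Goal setting will be measured at the baseline study visit, and the 12- and 24-month study visits"), social support, perceived benefit
- 3/8/24: glaucoma knowledge
- 3/12/24: depression, as listed in Table 2
- 0/12: question-asking confidence ("Confidence asking the physician questions will be assessed at the baseline visit and the 12-month study visit")

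**The concern.** Splitting a total effect into direct and indirect parts is coherent only if all the models describe the same records. A mixed model drops any record that lacks a covariate. The model with the mediator therefore shrinks to the two to four visits where that scale was given, while the model without it keeps all the adherence data. No rule is given for common records or for filling in the mediator between visits. The one remark on missing values in that section concerns the dependent series in the separate time-series analysis.

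The two time slopes then cover different calendars. Adherence is unlikely to follow a straight line here: the interventions are staged at months 3 and 6, and the plan itself allows for a fall after they end. At stake are the comparison of total with direct, their additivity, and any comparison of one mediator with another on a different schedule.

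**Working it through.** **Inputs from the protocol.** The three models and the schedules above; a gain from 70 to 80 points and an SD of 20 (Sample size). The protocol gives no figure for the mediation analysis. Its one related figure reproduces: SD of the difference = 0.20 × √(2 × (1 − 0.3)) = 0.2366; a two-sided 5% paired t test for a difference of 0.10 has power 0.801 at 46 participants.

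**Assumptions.** Mean adherence is 70 in months 1–3, 75 in months 4–6 and 80 from month 7. In year two it is sustained, falls in a straight line by 5 points (half decay), or falls by 10 (full decay). Each visit takes the adherence of the month ending at it. The month-0 visit takes month 1, because monitors are first handed out at that visit. The mediator drifts linearly and has no effect on adherence, so the expected direct slope is the plain slope on that mediator's visits.

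**Step 1: slopes.** Slope per year = 12 × Σ(t − t̄)(y − ȳ) / Σ(t − t̄)². For the sustained path:

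- all 24 months: 12 × 427.5 / 1150 = 4.46
- 0/6/12/24 (values 70, 75, 80, 80): 12 × 121.25 / 294.75 = 4.94
- 0/12 (values 70, 80): 12 × 55 / 60.5 = 10.91

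| Records | Sustained | Half decay | Full decay |
|---|---|---|---|
| Total, all 24 months | 4.46 | 1.96 | −0.54 |
| Total, six study points (0, 3, 6, 8, 12, 24) | 5.41 | 2.90 | 0.39 |
| Direct, 0/6/12/24 | 4.94 | 2.35 | −0.23 |
| Direct, 0/12/24 | 5.14 | 2.60 | 0.07 |
| Direct, 3/8/24 | 4.32 | 1.37 | −1.57 |
| Direct, 3/12/24 | 5.41 | 2.56 | −0.29 |
| Direct, 0/12 | 10.91 | 10.91 | 10.91 |

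**Step 2: total minus direct for a mediator that does nothing** (sustained, half decay, full decay).

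| Schedule | Total from 24 months | Total from six points |
|---|---|---|
| 0/6/12/24 | −0.48, −0.39, −0.31 | +0.47, +0.55, +0.62 |
| 0/12/24 | −0.68, −0.64, −0.61 | +0.27, +0.30, +0.32 |
| 3/8/24 | +0.14, +0.59, +1.03 | +1.09, +1.53, +1.96 |
| 3/12/24 | −0.95, −0.60, −0.25 | 0.00, +0.34, +0.68 |
| 0/12 | −6.45, −8.95, −11.45 | −5.50, −8.01, −10.52 |

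The true value is zero throughout.

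**Step 3: straight-line path.** At 5 points per year the raw slopes agree on every set of records. The standardized slope, (slope per month) × SD(time) / √(20² + variance of the mean path), does not, because SD(time) depends on the visits used. It is 6.92 months over all 24 months and between 5.50 and 9.39 on the mediator schedules. The standardized slope is 0.143 on all months and 0.114 to 0.192 on the mediator visits.

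**Step 4: simulation.** Random-intercept models, 46 participants, 1,000 runs per scenario, intraclass correlation 0.3 (assumed), SD 20, null mediator. With both adherence models on the mediator's visits, total minus direct lay between −0.02 and +0.04. Sobel's test rejected in 0.3% to 3.3% of runs at a nominal 5%.

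**Step 5: sensitivity.** With a second assumed path (65 in months 1–3, 72 in 4–6, 78 in 7–12, 74 in 13–24) and visits at their nominal months, the total is 2.68 on all months or 4.89 on the six points. The direct slopes are 4.17 (0/6/12/24), 4.50 (0/12/24), 3.16 (3/8/24), 4.65 (3/12/24) and 13.0 (0/12). Reading month 12 forward (74) rather than backward (78) changes the last figure from 13.0 to 9.0, so the adherence window matters too.

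**The case against.** The mismatch is inferred. The sentence about all time points describes the repeated-measures models in general, and the article does not say which records the mediator-adjusted model uses. Common rows and visit windows are details that a full plan often settles. This has some force. But the article itself fixes the data, the three equations, the standardization and their combination, and followed literally these conflict with its own questionnaire calendar.

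A narrower reading is that a time point means one of the six in the footnote to Table 2. That does not remove the mismatch, since no mediator is measured at more than four of the six. It does change the size and often the sign of the gap, so no single ratio of direct to total can be claimed.

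Two stronger readings are tempting and are not supported.

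- A reader might infer that the plan would declare mediation where there is none. It does not define the indirect effect as total minus direct. Its only named test is Sobel's, which uses the mediator-adjusted model and the mediator model, and both rest on the same visits. The simulation shows no inflation.
- A reader might infer that mediators will be ranked to steer the next trial. No ranking is planned. The Discussion speaks of feasibility and plausibility before a randomized trial.

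It also stands that the analysis is exploratory and that, for most scales, the gap is small beside an SD of 20.

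**Conclusion.** The point holds as a minor one. As written, total and direct effects are estimated on different records. They can differ for a mediator with no effect when the path is not straight, and on the standardized scale even when it is. Total, direct and indirect then need not add up, and the difference between total and direct is not evidence of mediation.

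Under the 70/75/80 paths with monthly adherence, the gap is about 0.1 to 1 point per year for three- and four-visit scales and 6 to 11 for the two-visit scale. On the six-point reading, or with the second assumed path, it reaches about 2 for the three- and four-visit scales. These figures rest on the assumed paths and on records without a mediator being dropped. A stated rule for filling mediators in between visits would change them. The Sobel test, the primary paired comparison and the sample size are not affected.

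**What to change.** For each mediator, fit all three models to the same person-visit records: the visits at which that mediator is measured, each linked to one stated adherence window. State the window for the month-0 visit explicitly, since no monitoring data yet exist then. Report the period each mediator covers, and do not compare effects between mediators with different schedules.

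This changes analysis wording only. The cost is fewer adherence records per mediator, so each total effect is less precise and describes only the period covered by that mediator's visits.

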**Methods:**

Glaucoma patients taking ≥ 1 medication will be pre-screened by telephone survey for adherence to their medication(s). Those who self-report poor adherence will be enrolled in a 3-month monitoring period to measure medication adherence using electronic medication monitors. Participants who are non-adherent (take </=80% of their medication doses) over the 3-month run in phase will be eligible for the study. We plan to enroll 57 participants who are non-adherent to their medications. Participants’ adherence will then be continuously measured with electronic medication monitors, by self-report, and via pharmacy refill data over 2 years, during which two successively more resource-intensive components of an intervention aimed to improve medication adherence will be administered. The first component is a 3-month period of reminders (audio and/or visual) and text message or automated phone call if a dose of medication is not taken within a pre-specified time frame. The second component is a 6-month MI-based counseling program with a trained glaucoma counselor. This component uses the *eyeGuide*, a computer-based personalized behavior change program that enables para-professional staff to provide personalized education and counseling for glaucoma. The primary outcome is change in medication adherence. The secondary outcomes include changes in clinical outcomes (intraocular pressure, IOP, and IOP fluctuation) and psychosocial mediators of adherence (e.g., competence, energy for change and satisfaction). Participants will undergo semi-structured interviews at 12 months to give feedback about the counseling program in order to improve it.

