An adherent event is defined as taking medication within a specified time window of a dose on the previous day. For a once daily medication, an adherent event is defined as taking the medication within 24 ± 4 h of the previous day’s dose. For a twice daily medication, an adherent event is defined as taking the first medication dose within 24 ± 2 h of the previous day’s first dose and taking the second medication dose within 24 ± 2 h of the previous day’s second dose. For a three times daily medication, an adherent event is defined as taking the medication dose (first, second, or third) within 24 ± 1.3 h of the previous day’s corresponding medication dose (first, second, or third). For a four-time daily medication, an adherent event is defined as taking the medication dose (first, second, third, or fourth) within 24 ± 1 h of the previous day’s corresponding medication dose. The biological efficacy of medications dosed multiple times daily declines when not taken on time [38–40]. However, when calculating adherence for medications dosed more than once a day, we compare the current day’s doses to the previous day’s corresponding doses rather than simply the previous dose (second versus first, or third versus second) as lifestyle and sleeping patterns can result in medication times that are not equally spaced. This method of calculating adherence also allows for large shifts (time zone changes for work or vacation) or gradual changes in times when medications are taken without overly penalizing the patient, which can happen when calculating adherence relative to a median time. Additionally, this method of measuring adherence ensures that adherence credit is not given for instances where bottles are opened numerous times just prior to a clinic visit [119]. For participants on more than one medication, adherence will first be measured at the medication level and then aggregated to the person level by dividing the total number of doses of all medication(s) taken on time by the total number of doses of all medication(s) prescribed. Baseline adherence will be calculated monthly during the 3-month monitoring period. The median monthly adherence will be designated as the baseline adherence score; choosing the median will help to mitigate the effects of regression to the mean. We will exclude patients from participating in the study whose median baseline adherence score is > 80% on all of their glaucoma medications after a baseline observation period of 3 months.

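### The logistic GEE for adherence of at least 80% includes run-in months held low by the 80% entry rule, so any time or period term in it is biased upward

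*Protocol article*

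**What the plan says.** Under Data analysis, the Protocol article uses linear mixed models (LMMs) to look for predictors of adherence and adds: "Repeated measures logistic regression with generalized estimating equations (GEE) will also be used to investigate predictors of adherence >/=80" (per cent). The candidate variables are given as follows: "Variables investigated will include participant characteristics and demographics, clinical measures of disease severity, and counseling and health literacy measures". For both kinds of model, "The repeated measures analyses (LMM and GEE) will use adherence data gathered over all time points". Electronic monitoring begins with the three-month run-in, so the run-in is among those time points.

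Under Baseline eligibility assessment, adherence is scored monthly in the run-in, the median of the three scores is the baseline, and "We will exclude patients from participating in the study whose median baseline adherence score is > 80% on all of their glaucoma medications". The abstract words the rule differently: "Participants who are non-adherent (take </=80% of their medication doses) over the 3-month run in phase will be eligible for the study". If a Hawthorne effect is found, the third month alone becomes the baseline score.

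The intervention test by slope is stated for the LMMs, at the start of the mediation series: "Because all participants receive the intervention, this will be a test of slope of medication adherence over time".

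The article does not say whether the GEE takes monthly rows or one score per period, or how time is coded. A fuller document may settle that, and its absence here is not the complaint.

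**The concern.** The same 80% cut is used twice: to decide who enters, from the run-in months, and to define the binary outcome, which includes those months. Run-in rows are thus selected on the outcome. Once the run-in ends the restriction lifts, and scores drift back towards each person's own level. A model with a time or period term reads that release as rising odds of adherence.

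The study has no control arm, which its Discussion names as its largest limitation, and it is meant to judge plausibility before a randomised trial. An odds ratio that rises because of the admission rule would mislead that decision. Using the median of three months reduces the influence of one odd month, but it does not undo selection on that median.

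**Working it through.** **1. The plan's own figure.** The article gives no number for the GEE. Its sample size reproduces: SD of the paired difference = 0.20 × √(2 × (1 − 0.3)) = 0.2366; for a difference of 0.10 at two-sided 5% (sidedness assumed), the noncentral t distribution gives n = 46 with power 0.801. Dropout: 46 / 0.8 = 57.5, against 57 stated.

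**2. What the entry rule fixes.** A median of three scores at or below 80% means at least two of the three are at or below 80%. So at most one run-in month in three can lie above the cut. The later months have no such cap.

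**3. Size with no intervention effect.** Monthly score = person mean + monthly noise, clipped to 0–1; entry if the run-in median is ≤ 0.80; 24 months. From the protocol: SD 0.20, n = 57, and 0.3 as the lower end of the correlation range (its pre-post value). Assumed: a mean of 0.70 before selection, 0.20 as the total SD before selection, and month-to-month correlation up to 0.9. The first two columns give the share of months at or above 80%. The odds ratio (OR) is [later / (1 − later)] / [run-in / (1 − run-in)]. The last two columns come from exchangeable logistic GEEs, 150 replicates per row.

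| Correlation | Run-in | Later | OR from shares | Follow-up vs baseline, p < 0.05 | Time slope significantly positive |
|---|---|---|---|---|---|
| 0.3 | 0.150 | 0.245 | 1.84 | 92% | 51% |
| 0.5 | 0.121 | 0.198 | 1.79 | 83% | 38% |
| 0.7 | 0.090 | 0.148 | 1.76 | 72% | 31% |
| 0.9 | 0.049 | 0.081 | 1.71 | 46% | 18% |

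The first row, for example, is (0.245 / 0.755) / (0.150 / 0.850) = 1.84. The fitted log odds ratios averaged 0.55 to 0.63, that is, odds ratios of about 1.7 to 1.9. Other simulations under comparable assumptions gave 21 to 50% and 27 to 36% for the last column. Without selection it was 2 to 4%, close to the 2.5% expected for positive results of a two-sided 5% test.

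**4. Other means.** With a pre-selection mean of 0.6 or 0.8, the shares go from 0.095 to 0.136 (mean 0.6, correlation 0.3; OR 1.50) up to 0.201 to 0.374 (mean 0.8, correlation 0.3; OR 2.37). The direction is the same throughout.

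**5. One median score per period.** In one simulated null trial (correlation 0.5) the events were 0, 4, 10 and 3 of 57 in the four periods. With categorical period the fit ran off: intercept −26.6, period coefficients +23.7 to +25.0. A linear time slope stayed finite (0.034 per month).

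**6. Predictors.** With monthly rows an example odds ratio moves from 1.67 without the run-in to 1.63 with it. With one score per period it moves from 1.96 to 1.83; ln 1.83 / ln 1.96 = 0.604 / 0.673 = 0.90, about 10% on the log scale.

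**7. The LMM slope.** On the continuous scale under no effect, the mean run-in median of 0.631 becomes a later mean of 0.664 at correlation 0.3, and 0.602 becomes 0.607 at 0.9. Per-person least-squares slopes, as a stand-in for the LMM, were falsely significantly positive in 25% of trials at correlation 0.3, 13% at 0.5 and 5% at 0.9.

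**8. The remedy.** With the GEE outcome starting at month 3, the false-positive share was 1 to 5%. With the run-in median also entered as a covariate it was 1 to 4%.

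**The case against.** The best defence is that the GEE is there to find predictors, that its listed variables do not include period, and that the slope test belongs to the LMMs. This stands in part: predictor odds ratios are hardly affected, and the bias bites only if a time or period term is fitted. Yet a repeated-measures model spanning run-in, two intervention phases and follow-up can hardly do without one. A counselling variable that changes over time, if used, would also act like a period term.

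A reader might infer more than the documents support, in two ways.

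- **That the run-in outcome is zero for everyone and period effects cannot be estimated.** The rule caps the median, not each month. In step 3, 5 to 15% of run-in months are events, and every monthly fit gave a finite period effect. The wording about all medications loosens the cap further: read literally, someone at 95% on one once-daily drug and 78% on another enters with a person-level score of (95 + 78) / 2 = 86.5%. Separation needs one median score per person and categorical period; the article states neither for the GEE.
- **That selection turns a true decline into an apparent rise.** With assumed gains of 10, 10 and 6 points by phase, the slope is positive with the run-in and negative without it. But the same happens with no selection at all (+0.016 against −0.031 per month), because those gains rise and then fall. Adherence in every later phase then truly exceeds baseline, so the positive slope is not false.

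The authors do acknowledge regression to the mean and the missing control arm. That acknowledgement concerns the baseline score and the design; it does not take the selected months out of the outcome.

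**Conclusion.** The concern holds in this limited form. The run-in months are outcome rows in a logistic model cut at the entry threshold, so time and period terms are biased upward. With monthly data and no intervention effect, the spurious later-versus-baseline odds ratio is about 1.7 to 1.9, and the time slope is falsely significantly positive in roughly 20 to 50% of trials. These sizes rest on the assumed pre-selection mean, the use of 0.20 as the pre-selection SD, and the correlation range. The upward direction follows from the entry rule and appeared in every setting tried. Non-finite period effects are conditional on the single-score, categorical-period reading. Harm to the stated aim, finding predictors, is small. The LMM slope is affected in the same direction, less so as months correlate more strongly.

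**What to change.** Start the GEE outcome at month 3 (reminder, eyeGuide and post-intervention periods), enter the run-in adherence score as a continuous baseline covariate, and say whether rows are monthly or per period. Do the same in LMMs used only to find predictors.

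Do not extend this to the LMM slope test of the intervention or to the mediation series, which would lose their pre-intervention period. Keep the run-in there, state that it was selected on the outcome so that part of any rise is regression to the mean, and report a sensitivity analysis without the run-in months.

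The cost is a row filter, a few sentences and one extra analysis. The GEE would no longer give a baseline-to-later odds ratio. With monthly rows that ratio can be computed, so something is given up, but selection biases it in any case.

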## Methods/design

In order to test the preliminary impact of the personalized eHealth intervention among non-adherent glaucoma patients, we will electronically monitor medication adherence longitudinally over 2 years. The two main components to be evaluated are (1) real-time automated adherence reminders using commercially available AdhereTech electronic medication monitors (AdhereTech, New York, USA) and (2) in-person tailored counseling with a medical assistant trained in MI (the eyeGuide program). Adherence will be monitored for all patients for a total of 2 years. Adherence will first be monitored for a 3-month period prior to the intervention to obtain baseline adherence and mitigate issues with regression to the mean and the Hawthorne effect [37]. Adherence will then be measured over a nine-month period of time during which the two interventions will be sequentially administered. Finally, adherence will be measured for 1 year after the conclusion of intervention to assess how well change in adherence is maintained over time.

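### The exploratory mediation models, and the moderator interactions resting on the same slope, represent the intervention effect by one slope over all 24 months, which mixes change during the intervention with maintenance after it

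*Protocol article*

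**What the plan says.** The mediation analysis in the Data analysis section is a series of three linear mixed models. Its opening step is stated as "First, the effect of the intervention on glaucoma medication adherence will be tested", and the article explains how: "Because all participants receive the intervention, this will be a test of slope of medication adherence over time". The models are written out. Adherence is regressed on time, then on time plus the mediator, and finally the mediator is regressed on time. Time is the only term standing for the intervention. The results are then carried forward: "the direct, indirect, and total effects of the intervention will be estimated and Sobel’s test will be used".

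Moderators use the same slope: "Moderators of glaucoma medication adherence will be investigated in the LMMs by interactions with time", the purpose being "to test the hypothesis that moderators will have different slopes of medication adherence over time". On which data enter, the article says: "The repeated measures analyses (LMM and GEE) will use adherence data gathered over all time points".

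Methods/design and Timeline give the time axis. "Adherence will be monitored for all patients for a total of 2 years", made up of a 3-month run-in, 3 months of reminders, 6 months of eyeGuide counselling, and then "adherence will be measured for 1 year after the conclusion of intervention".

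**The concern.** The design is off, on, on, off, and its second half lies after the intervention has stopped. A straight line through all of it does not isolate what happened while the intervention was delivered. A gain that wanes after month 12 pulls the slope down, and a change that begins only after month 12 pushes it up. The Data analysis section itself foresees a fall after the intervention, and Methods/design treats maintenance as a separate question. One slope answers neither question cleanly, and it cannot separate reminders from counselling.

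At stake are the analyses of why and for whom the intervention works, in a pilot meant to prepare a randomized trial. If the total effect, or the path from intervention to mediator, is near zero or has the wrong sign, the indirect effect and its test are affected too.

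**Working it through.** **The plan's own figure.** The Sample size section uses 0.70 to 0.80, SD 0.20 and correlation 0.3. The SD of the difference is 0.20 × √(2 × (1 - 0.3)) = 0.2366. A two-sided 5% paired t test for a difference of 0.10 then needs n = 46 (power 0.801), as stated. Dividing by 0.8 gives 57.5 against the planned 57. The calculation is sound, but it powers a pre-post difference and not a slope.

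**How the slope weights the periods.** Take 24 monthly values, t = 1 to 24, with mean 12.5. The slope is Σ(t - 12.5)y / Σ(t - 12.5)², and the denominator is 1150. The summed weights are:
- run-in: 3 × (2 - 12.5) = -31.5
- reminders: 3 × (5 - 12.5) = -22.5
- eyeGuide: 6 × (9.5 - 12.5) = -18
- post-year: 12 × (18.5 - 12.5) = +72

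Every month of the intervention carries a negative weight. With the other periods held fixed, better adherence during reminders or eyeGuide lowers the slope. Only the post-year raises it.

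**Profiles with a real 10-point gain.** Run-in 70 and eyeGuide 80 come from the protocol; 75 under reminders is assumed. As deviations from 70, the two intervention periods contribute -22.5 × 5 - 18 × 10 = -292.5.

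| Post-year | Numerator | Slope per month | Over 24 months | eyeGuide minus run-in |
|---|---|---|---|---|
| Kept at 80 | -292.5 + 720 = 427.5 | +0.372 | +8.9 | +10 |
| Half lost, 75 | -292.5 + 360 = 67.5 | +0.059 | +1.4 | +10 |
| Linear fade to 70 | -292.5 + 210.8 = -81.7 | -0.071 | -1.7 | +10 |
| Lost at once, 70 | -292.5 | -0.254 | -6.1 | +10 |

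For the fade, the post-year term is Σ(k - 0.5)(10 - 10k/12) over k = 1 to 12, that is 720 - 509.2 = 210.8. The slope is zero at a post-year mean of 70 + 292.5/72 = 74.1, still about 4 points above run-in.

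**Profiles with no effect during the intervention.**
- A 10-point rise only after month 12: 720/1150 = 0.626 per month, +15.0 over 24 months. The period contrast is 0.
- Drift of 0.2 per month: slope +4.8 over 24 months; contrast 0.2 × (9.5 - 2) = +1.5.
- A 5-point shift after run-in, as from regression to the mean: 5 × 31.5/1150 = 0.137, or +3.3 over 24 months; contrast +5.

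**Rejection rates, n = 46, by simulation.** The documents give no split of variance within and between periods, so two were tried. Split A has person SD 11, person-by-period SD 15.5 and monthly SD 10 points. Its SD for the eyeGuide minus run-in difference, √(2 × 15.5² + 10²/3 + 10²/6) = 23.0, is close to the plan's 23.7. Split B applies SD 20 and correlation 0.3 to each monthly value.

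| Scenario | Slope, split A | Slope, split B |
|---|---|---|
| Gain kept | 57% positive | over 99% positive |
| Half lost | 6% positive | 12% positive |
| Linear fade | 1% positive, 6% negative | under 1% positive, 16% negative |
| Lost at once | 31% negative | 92% negative |
| Late rise only | about 95% positive | 100% positive |

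In the first four rows the period contrast detects the gain in about 82% (A) or about 100% (B). In the late-rise row it is significantly positive in about 2.5%.

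**Coarser data.** With four period means placed at months 3, 6, 12 and 24, immediate loss still gives a negative slope (-0.07 per month), but linear fade gives +0.15.

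**A mediator.** Take values 0, 0.5, 1, 0 at months 0, 6, 12, 24. The mean time is 10.5 and the sum of squares 315. The slope is (-4.5 × 0.5 + 1.5 × 1)/315 = -0.0024 per month, or -0.06 over 24 months. A mediator that rose throughout the intervention shows a path of about zero.

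**The case against.** The best defence is that little depends on these models. The article says moderators and mediators will be explored, and Table 2 is labelled exploratory. The primary effect comes from paired t tests of baseline against post-intervention adherence, which is already a period comparison. Changes in glaucoma skills and energy for change are tested by paired tests after each component. The time-series model adjusts for study intervention period and looks for a fall after the intervention, and one-year stability is examined separately. All of this stands, and it limits the point to the mediation and moderator models.

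Four stronger readings are tempting and are not supported.
- A reader might infer that the primary result is compromised. It is not, because it does not use the slope.
- A reader might infer that any loss after month 12 cancels the gain. With half lost, the slope is still +1.4; a negative sign needs a larger loss, and under linear fade it depends on how finely the data are entered.
- A reader might infer that every mediator is modelled over 24 months. Confidence in asking the physician questions is measured only at baseline and 12 months, so its slope is simply that change. The moderator sentence speaks only of different slopes; it shares the problem because it relies on the same slope.
- A reader might infer that false positives from background change are all due to the slope. Under split A, a 10-point drift gives a significant slope in 65 to 71% of trials and a significant contrast in about 15%. A 5-point regression-to-the-mean shift gives about 12% for the slope and 30% for the contrast, so there the contrast does worse. The cause is the missing control arm, which the Discussion names as the largest limitation.

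What remains is specific to the slope coding: loss of power or reversal of sign when a real gain wanes, and a positive result when change starts only after the intervention ends.

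**Conclusion.** The point holds for the exploratory mediation models and for the moderator interactions that rely on the same slope. The article fixes the regressor and calls its slope the intervention effect, so this is a stated rule that does not fit the design, and not detail left to an analysis plan. For the same 10-point gain during eyeGuide, the slope over 24 months runs from +8.9 to -6.1 points according to what happens after month 12.

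The slope values rest on monthly data, the protocol's 70% and 80%, an assumed 75% under reminders, and assumed waning. The documents do not say how much adherence will wane; if most of the gain persists, the slope keeps its sign and mainly loses power. The rejection rates depend strongly on the assumed variance split (31% against 92% for immediate loss), so they show direction and not a forecast. This should be fixed before the analysis, but no primary result depends on it.

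**What to change.** In the three mediation models and the moderator interactions, replace linear time by the four-level study period: run-in, reminders, eyeGuide, post-year. Define the intervention effect as eyeGuide minus run-in, with reminders minus run-in second, and report post-year minus eyeGuide as maintenance. Test moderators as interactions with those contrasts.

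For each mediator, use only the contrasts that its visits support. Scales given at 0, 6, 12 and 24 months allow most of them. Goal setting (0, 12, 24) allows 0 to 12 and 12 to 24. Confidence in asking the physician questions allows 0 to 12 only. Glaucoma knowledge (3, 8, 24) allows 3 to 8 and 8 to 24, and the 3-to-8 change spans reminders as well as the start of eyeGuide.

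The data and software stay the same, and the period variable is already planned for the time-series model. The cost is a few parameters: a four-level factor uses three where the slope uses one, so two more per mediation model and about two more per moderator interaction. Some mediators will support fewer contrasts than others. The report should say that regression to the mean and secular drift remain. A bootstrap interval in place of Sobel's test and within-person centring of mediators are optional and not part of this defect.
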